### 2.17 Data and sample collection

Three study members were trained to master the criteria and methods of case collection to minimize the selection bias. During data collection, the medication of participants was recorded in detail, and the interference and contamination factors in the statistical analysis were excluded.

On the consent form, the participants were asked if they agreed with the use of their data or they chose to withdraw from the trial. This trial does involve collecting biological specimens for storage. All samples were destructed after use.

### 2.18 Data management and monitoring

An independent Data and Safety Monitoring Board has been established to monitor the conduct and safety of the study. Two members of the research group (YH and XZ) entered the collected information into the Chinese Clinical Trial Management Public Platform under a confidential condition. The hard copy records were preserved at a locked office. No one will be able to change or use the hard copy and electronic data without the authorization of our group.

The investigators did their best to avoid missing clinical trial data. In the process of dealing with missing data, we chose different processing methods, according to the judgment of data managers on the mechanism of missing data. At the same time, it is necessary to make a sensitivity analysis of the test results.

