### 2.7 Handling of withdrawal and data management

Participants can withdraw from the study at any time. If any participant stops using study medication or takes other medications that may affect the results during the study, the participant will not be a part of the study anymore. Participants failed to follow up and ones withdrawn from the study were recorded and reported. Incomplete data will be cleaned up if less than 5–10% of participants withdraw from the study. Missing data will be processed through data imputation, intention to treat analysis, and sensitivity analysis if greater than 10% participants withdraw from the study.

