### 2.16 Sample size

According to the sample size estimation method for the comparison of two sample means, we preset the sample size of the placebo group and the intervention group for them to be equal. The calculation formula is as follows:
$$n=2\sigma^{2}\times \frac{f\left(\alpha ,\beta \right)}{{\left(\mu_{1}-\mu_{2}\right)}^{2}},$$

where *n* represents the overall sample size of the study, μ1 and μ2 are the mean values of the control group and the test group, respectively, and σ is the standard deviation. We set that the probability of making type I error in this study shall not be greater than 5%, and the probability of making type II error at the same time shall not be greater than 10%, that is, α = 0.05 and β = 0.1. Referring to Chinese literature reports on TCM external washing for the treatment of postoperative wound of anal fistula, the wound healing rate (%) in literatures was set as the clinical efficacy observation, the mean value was 33.35, and the standard deviation was 2.29 in the intervention group, and the mean value was 27.33 and the standard deviation was 2.67 in the placebo group. The estimated loss of the follow-up rate was 20%, so the total study sample size was 60, of which 30 was for the intervention group and 30 was for the placebo group.

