### 2.20 Data analysis

All data analyses were conducted by SPSS 24.0 software. Student’s t-test was performed on continuous normally distributed variables, the Wilcoxon rank-sum test on non-normal variables, and Pearson’s χ^2^ test on categorical variables. Data were presented as the mean ± standard deviation for continuous variables or percentage values for categorical variables. The statistical significance level was set at *p* < 0.05, and all the statistical tests were two-sided.

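### Sections 2.7 and 2.18 give two unreconciled rules for missing data, and neither fixes the choice of method before unblinding

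*Protocol article*

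**What the plan says.** Section 2.7 works by withdrawal percentage. Its lower branch reads "Incomplete data will be cleaned up if less than 5–10% of participants withdraw from the study". Its upper branch reads "Missing data will be processed through data imputation, intention to treat analysis, and sensitivity analysis if greater than 10% participants withdraw from the study". The same section says of anyone who stops study medication, or takes other medication that may affect the results, that "the participant will not be a part of the study anymore".

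Section 2.18 covers the same data with no percentage: "we chose different processing methods, according to the judgment of data managers on the mechanism of missing data". It then adds "At the same time, it is necessary to make a sensitivity analysis of the test results".

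Section 2.20 names the tests ("Student’s t-test was performed on continuous normally distributed variables, the Wilcoxon rank-sum test on non-normal variables", and a chi-square test for categorical data) and does not mention missing data. Section 2.16 plans for substantial loss: "The estimated loss of the follow-up rate was 20" per cent, with 60 participants in total and 30 per arm.

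**The concern.** The two sections differ on what selects the method (the share who withdraw, or a judgement about the mechanism) and on when a sensitivity analysis is run (above 10%, or with no threshold). Under 2.7, even the use of intention to treat depends on the withdrawal rate observed.

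The 2.18 criterion cannot be applied objectively. Whether values are missing at random or not at random turns on the values that were not seen, so two careful data managers could look at the same records, disagree, and choose different methods. Neither section says when the judgement is made or whether it is made blind. At stake is whether the primary comparison follows one pre-specified analysis or one of several chosen once data are available.

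**Working it through.** **The two rules side by side**

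| | Section 2.7 | Section 2.18 |
|---|---|---|
| What selects the method | Percentage withdrawn | Data managers' view of the mechanism |
| Intention to treat | Tied to more than 10% withdrawn | Not mentioned |
| Sensitivity analysis | Tied to more than 10% withdrawn | Necessary, no threshold |
| Timing or blinding of the choice | Not stated | Not stated |

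At 8% withdrawal, for example, 2.18 calls for a sensitivity analysis and 2.7 does not provide for one.

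**Gaps within 2.7.** With 60 participants, 5%, 10% and 20% are 3, 6 and 12 people. The upper branch starts at 7. If the lower limit is read as 5%, the lower branch ends at 2 and counts of 3 to 6 have no rule. If it is read as 10%, the lower branch ends at 5 and a count of exactly 6 has no rule.

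**Which branch to expect.** Take withdrawals X as binomial with n = 60, treating the planned loss as the withdrawal probability.
- True rate 20% (section 2.16): P(X ≤ 6) = 0.031, so P(X ≥ 7) = 0.969.
- True rate 10%: P(X ≥ 7) = 0.394.
- True rate 5%: P(X ≥ 7) = 0.030.

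**Can the method change the verdict?** An illustration with assumed missingness: 6 of 30 missing per arm, and the SD pooled from section 2.16, √((2.29² + 2.67²)/2) = 2.487.
- Complete cases, observed difference 1.5 points: SE = 2.487 × √(2/24) = 0.718, t = 2.09 on 46 df, p = 0.042.
- Missing intervention values set at the control level: difference 0.8 × 1.5 = 1.2, SE = 2.487 × √(2/30) = 0.642, t = 1.87 on 58 df, nominal p = 0.067.
- At the planning difference of 33.35 − 27.33 = 6.02 points, the same two calculations give t = 8.38 and t = 7.50, so the verdict does not change between them. Other methods, such as last value or zero healing, could reduce power considerably there.

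**Worst-case error rate.** Simulation with no treatment effect and 30 per arm. Assumed: mean healing of 25, 50, 70 and 85% at weeks 1 to 4, between-person SD 8, within-person SD 6, and 20% missing completely at random at week 4 with a random last-seen week. Test: two-sided t-test at 0.05.

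| Analysis | False positives |
|---|---|
| Complete cases | about 5% |
| Last value carried forward | about 5% |
| Zero healing for missing | about 5% |
| Single arm-mean imputation | about 12% |
| Smallest p of the first three | about 11% |
| Smallest p of all four | about 17.5% |

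The last two rows count significance in either direction. In favour of JSD alone they are about 5.6% and 9%, against a nominal 2.5%.

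**The plan's own total.** The formula in 2.16 gives 2 × 2.487² × (1.960 + 1.282)² / 6.02² = 3.59, so 4 per arm, or 10 in total after 20% loss. It does not reproduce 60. That is a separate matter and does not affect this point.

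**The case against.** The two sections can be read as complementary: 2.7 says when missing data get formal treatment, and 2.18 says how the method is then picked. On that reading the sensitivity-analysis sentence in 2.18 applies only once missing data are being handled. This is a fair reading and removes part of the conflict. But neither section says so or refers to the other, and the sensitivity-analysis condition is still not stated consistently.

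A reader might infer that the method will be picked after outcomes by arm are known. The article does not say that. Section 2.10 states that researchers had no group information, and a blinded choice could not be steered towards JSD. Equally, 2.18 does not require blinding, and 2.9 gives the project leader a copy of the allocation table. What stands is that the timing is open.

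A reader might also infer that 12 of 60 participants will have primary values set by the chosen method. That does not follow. The 20% is overall loss to follow-up, and follow-up runs to 16 weeks after treatment. Those lost late would already have weekly wound measurements, and some would have an observed healing time. A complete-case analysis sets no values at all.

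Finally, naming an imputation method or model is commonly left to a statistical analysis plan, which is not at hand. Its absence is not the point here. The point is that the article itself states two rules that do not agree and gives the choice to a judgement.

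**Conclusion.** The point holds as a conflict of wording with a real analytic consequence, and it should be fixed. The rules as written let the analysis set, the primary method and the presence of a sensitivity analysis depend on observed withdrawals and on a judgement that the data cannot settle. At the planned loss the upper branch of 2.7 applies with probability 0.97, so the choice will very probably be needed.

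The effect on the result is possible, not shown. For a modest observed difference the method can move p across 0.05 (0.042 against 0.067 in the illustration). At the planning difference it did not for the two methods compared.

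The 11% and 17.5% should not be read as the trial's expected false-positive rate. They need an unblinded pick of the smallest p in either direction, assumed trajectories and SDs, and all loss falling by week 4. The higher figure also needs arm-mean imputation, which the article nowhere names. Choosing complete cases, last value or zero healing without regard to the result keeps about 5% in the same simulation.

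**What to change.** Replace the missing-data text in 2.7 and 2.18 with one rule, fixed before unblinding:

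- Analyse all randomised participants as assigned, whatever the withdrawal rate.
- Pre-set one primary method per type of outcome. For the repeated continuous outcomes, use a mixed model for repeated measures on the baseline and weekly values already collected. It too assumes a missingness mechanism, which should be stated. It does not cover healing time or pathogen distribution, so pre-set a method suited to each.
- Always run one pre-set sensitivity analysis that departs from the main missing-data assumption, for example by making missing JSD values progressively worse than the model predicts.
- Have data managers record reasons for missingness, but not choose the method.

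This costs changes of wording and modest extra analysis, with no new data. The downside is less flexibility if the missingness pattern turns out to be unusual.

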### 2.19 Adherence to study interventions

During the study, we provided clear oral and written instructions to encourage and monitor the interventions. If necessary, further personalized guidance was provided. All unused medication was returned and recorded.

### 2.20 Data analysis

All data analyses were conducted by SPSS 24.0 software. Student’s t-test was performed on continuous normally distributed variables, the Wilcoxon rank-sum test on non-normal variables, and Pearson’s χ^2^ test on categorical variables. Data were presented as the mean ± standard deviation for continuous variables or percentage values for categorical variables. The statistical significance level was set at *p* < 0.05, and all the statistical tests were two-sided.

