### 2.2 Study population

Patients were recruited from three hospitals: the Affiliated Hospital of Chengdu University of Traditional Chinese Medicine, Yanjiang District Hospital of Traditional Chinese Medicine in Ziyang City, and Chengdu Anorectal Specialized Hospital.

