### 2.5 Inclusion criteria

1. Confirmed diabetes mellitus (Alberti and Zimmet, 1998) with postoperative anal fistula.

The diagnostic criteria for anal fistula refer to the guidelines for Clinical Diagnosis and Treatment of Anal Fistula (2006 Edition) jointly formulated by the Colorectal and Anal Surgery Group of Chinese Society of Surgery, Anorectal Branch of Chinese Society of Traditional Chinese Medicine, and Specialized Committee of Colorectal and Anal Diseases, Chinese Association of Modern Medicine.2. Aged 18 to 75.3. 4cm^2^ ≤ postoperative wound area<30 cm^2^.4. TCM syndrome differentiation is dampness–heat blood stasis syndrome, referring to the People’s Republic of China Industry Standard for Traditional Chinese Medicine Diagnosis and Efficacy Criteria for Anal Leakage Syndrome.5. No previous surgery for anorectal disease and no abnormal anal morphology or function.6. Voluntary participation and signed informed consent.

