### 2.12 Primary outcomes

#### 2.12.1 Wound healing

Assessments were at T0, T1, T2, T3, and T4. At the same time, weekly assessments were conducted during weeks 1–4 of intervention.1) Wound healing rate: The wound area on the first postoperative day was the original area. The maximum length and width of the wound were measured with the calculated area. Formula: Wound healing rate = (original area-current area)/original area × 100%.2) Wound healing time: From the start of the dressing change to the complete epithelialization and healing of the wound.3) Wound secretion score (Table 2) (Gould et al., 2021): Wound with abundant secretion, two or more pieces of penetrated gauze, dressing change more than twice a day, 3 points; wound with much secretion, one piece of penetrated gauze, dressing change twice a day, 2 points; wound with little secretion, no penetrated gauze, 1 point; and wound with smooth surface and no obvious secretion, 0 point.4) Wound edema score (Table 2) (Gould et al., 2021): Wound with severe edema which is significantly more than the wound edge, surgical resection needed, 3 points; wound with obvious edema which is more than the wound edge, need dressing change to remit, 2 points; wound with mild edema, 1 point; and wound with no edema, 0 point.5) Granulation tissue color score (Table 2) (Gould et al., 2021): Bright red, 1 point; light red, 2 points; and purple, 3 points.6) Anal function evaluation: The Wexner incontinence score was used to evaluate the anal function of participants after wound healing (Zhang et al., 2020a), including the ability of the anus to control the intestinal fluid, bowel gas, and loose and formed stools.7) Anal pain score: The pain index tested before the dressing change on the first postoperative day was the baseline pain. The pain index after the first postoperative day was tested within 2 h after the dressing change. Pain values were tested using the visual analogue scale (Anal pain visual analogue scale, VAS) (Bondi et al., 2017).

**TABLE 2 T2:** Scale for assessing wound healing.

Wound secretion score (Gould et al., 2021)	Score
Would with smooth surface and no obvious secretion	0
Would with little secretion and no penetrated gauze	1
Wound with much secretion, one piece of penetrated gauze, and dressing change twice a day	2
Wound with abundant secretion, two or more pieces of penetrated gauze, and dressing change more than twice a day	3
Wound edema score (Gould et al., 2021)	Score
Wound with no edema	0

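### Section 2.20 tests continuous outcomes without adjusting for original wound area, own baseline or centre, which gives away precision but does not invalidate the comparison

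*Protocol article*

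**What the plan says.** Section 2.20 assigns tests by type of variable: "t-test was performed on continuous normally distributed variables, the Wilcoxon rank-sum test on non-normal variables", and a chi-square test for categorical data. It names no covariate, baseline value or centre term.

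Other sections show what is available for adjustment:

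- **Original wound area.** Section 2.12.1 records it for every patient: "The wound area on the first postoperative day was the original area". Inclusion criterion 3 (section 2.5) admits areas from 4 cm² upward, with the upper limit given as "postoperative wound area<30 cm" squared.
- **Own baseline.** The wound assessments in section 2.12.1 and the lipids and SF-36 in section 2.13 are scheduled at T0. Section 2.12.1 defines a baseline pain value for the VAS.
- **Centre.** Section 2.2: "Patients were recruited from three hospitals". Section 2.9 describes the allocation of 60 participants and mentions no stratification.

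The protocol treats wound size as prognostic. The Introduction links a large postoperative wound surface to infection and long healing, and the Discussion says that large wounds in diabetic patients heal with difficulty.

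**The concern.** An unadjusted t-test leaves all outcome variation explained by baseline in the error term. Eligible wounds span a 7.5-fold range (30/4), and the protocol's own rationale says that size affects healing. Part of the between-patient variation should therefore be predictable from data already in hand.

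Dividing by original area, as the healing rate does, need not remove that dependence. Healing time, also listed among the primary outcomes, is not scaled by area at all.

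At stake is the width of the confidence interval, and how far an unlucky split of wound sizes or hospitals can move the estimate in a trial of 60 patients. The Discussion names small sample size as a limitation. Unused baseline information is the cheapest way to ease it.

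**Working it through.** **Inputs from the documents.** Section 2.16: "α = 0.05 and β = 0.1"; "the mean value was 33.35, and the standard deviation was 2.29 in the intervention group"; "the mean value was 27.33 and the standard deviation was 2.67 in the placebo group"; 20% loss; 30 per arm. Section 2.20: "all the statistical tests were two-sided". The correlation between baseline and outcome is not given, so I assume r = 0.3, 0.5 and 0.6.

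**Step 1: the plan's own figure.** Difference = 33.35 − 27.33 = 6.02. Pooled SD = √[(2.29² + 2.67²)/2] = 2.487. Two-sided, n per arm = 2 × 2.487² × (1.960 + 1.282)² / 6.02² = 3.6, so 4 per arm, or 5 after 20% loss. The stated 30 per arm does not follow from these inputs. That is a separate matter. It counts here only because it shows how generous the trial is on its own assumptions.

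**Step 2: chance variation without adjustment.** Evaluable per arm = 30 × 0.8 = 24. SE = 2.487 × √(2/24) = 0.72. The 95% chance range of the whole difference is ±1.96 × 0.72 = ±1.41 points. The target is 6.02/0.72 = 8.4 SEs, and power exceeds 99.9%.

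**Step 3: the part due to a covariate.** The 95% shift from chance imbalance in a baseline variable is 1.96 × r × 0.72. Adjustment multiplies the residual variance by 1 − r², so 24 per arm act like 24/(1 − r²).

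| Assumed r | Variance removed | 24 per arm acts like | SE, points | 95% shift from imbalance, points |
|---|---|---|---|---|
| 0 | 0% | 24 | 0.72 | 0 |
| 0.3 | 9% | 26.4 | 0.68 | ±0.42 |
| 0.5 | 25% | 32.0 | 0.62 | ±0.70 |
| 0.6 | 36% | 37.5 | 0.57 | ±0.84 |

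The factor ignores the few degrees of freedom spent on covariates, so the net gain at r = 0.3 is somewhat below 9%.

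**Step 4: if the SDs are too narrow.** For the ±95% chance range to reach 6.02 points at 24 per arm, the SD would have to be 6.02/(1.96 × √(2/24)) = 10.6, over four times the stated value. With an SD of 10 (assumed), power at 24 per arm would be 53% unadjusted and 57%, 65% and 72% at r = 0.3, 0.5 and 0.6. Adjustment pays most where the planning SD proves optimistic.

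**Step 5: a geometric check.** Assume square wounds, areas spread over 4 to 30 cm² (uniform in area, in log area or in side length), and the same 2 mm advance from each edge. Wound size alone then gives the healing rate an SD of 5.4 to 6.3 points, and the 95% range of imbalance between arm means is ±3.1 to ±3.6 points. In simulation, imbalance exceeded 6.02 points in roughly 0.1% of trials or fewer. With a 3 mm advance the SD is 7.5 to 8.7, the range ±4.3 to ±4.9, and the share about 0.6% to 1.7%. These SDs are two to three and a half times those in section 2.16, so the model cannot be combined with the protocol's planning figures.

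**The case against.** The strongest reply is that nothing is wrong with the tests. Randomisation makes the unadjusted comparison valid, chance imbalance is already in its standard error, and on the stated inputs power exceeds 99.9% either way. All of this stands, and it limits the point to precision.

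A reader might infer that chance imbalance could swamp the 6-point target. The tempting arithmetic is that a 2 mm edge advance closes 1 − (1.6/2.0)² = 36% of a 2.0 cm square wound but 1 − (5.0/5.4)² = 14% of a 5.4 cm one, a 22-point gap. That gap is between two single patients near the extremes of eligibility, while 6.02 is a difference between arm means. Steps 2 and 5 show that the inference fails on the protocol's SDs and is very unlikely under the edge-advance model itself.

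A reader might also infer that percentage healing depends strongly on wound size. The documents say only that large wounds heal slowly. They give no correlation, and the healing rate already has original area as its denominator.

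Finally, an article condenses a fuller plan, and covariates may be fixed in an analysis plan that is not shown. This stands in part: the lack of a stratification description or of visit-level modelling detail is no finding. But section 2.20 does not leave the test open. It names an unadjusted one, and that stated choice can be improved.

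**Conclusion.** The point holds as a question of efficiency. The plan names unadjusted tests where adjusted ones would use original wound area, own baseline and centre at almost no cost. The gain is 9% to 36% of residual variance under assumed correlations of 0.3 to 0.6, and it would be little or nothing if baseline predicts outcome weakly.

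The planned healing-rate comparison is not at risk on the protocol's figures: ±1.4 points of total chance variation against 6.02. The benefit matters mainly if the true SD is well above 2.29 to 2.67, and for the other continuous outcomes, for which no planning figures are given. The documents do not support calling the unadjusted analysis biased or invalid.

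**What to change.** In section 2.20, make the prespecified analysis of the continuous outcomes at the primary visit (T1 in section 2.11) an ANCOVA with:

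- treatment;
- log original wound area;
- centre (three hospitals);
- the outcome's own baseline where one exists (VAS, lipids, SF-36).

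Fix the covariates before unblinding, since adding them later would look data-driven. Keep the unadjusted t-test or rank-sum test as a sensitivity analysis. If a fuller analysis plan already specifies adjustment, bring section 2.20 into line with it.

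A repeated-measures model is optional. With seven post-baseline visits (weeks 1, 2, 3, 4, 8, 12 and 16 in the Abstract), an unstructured covariance has 7 × 8/2 = 28 parameters to estimate from about 48 patients, and percentage healing is bounded at 100%. A Gaussian model should not be applied to the three- and four-level secretion, edema and granulation scores, or to healing time.

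Cost: a change of wording and a standard SPSS procedure on data already collected. One covariate for area, two for centre and one for own baseline take 4 of the 46 residual degrees of freedom available with 24 per arm.
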